### Exercise training programme

The CR programme may consist of the following supervised outpatient treatment modules: exercise training, an information programme, a relaxation programme, a smoking cessation programme, a psycho-educative prevention programme and/or individual treatment by a psychologist or dietician. Based on the individual needs assessment procedure, one or more of these treatment modules are selected [23]. Treatment goals and results of the needs assessment are registered in the Hospital Information System by the nurse specialist. In both treatment groups, the CR programme consists of at least the exercise training module. The exercise training programme in both the intervention and control group is composed according to evidence-based clinical algorithms for the prescription and evaluation of exercise-based CR [26]. These algorithms serve as best practice standards in the Netherlands and were developed using recent Dutch and European CR guidelines and position statements. The content of the programme is determined individually, based on the referral diagnose, training goal(s) and physical fitness level. The programme may consist of several training modalities, including aerobic training (continuous training (CT) or high-intensity interval training (HIT)), functional training and resistance training. In aerobic training, the training frequency ranges from 2–5 sessions per week, lasting 20–60 min at 50–80% (CT) or 80–90% (HIT) of the heart rate reserve (HRR). We expect aerobic training to be similar in both treatment groups in terms of duration, frequency and intensity.

### Control group (centre-based cardiac rehabilitation)

Patients in the control group participate in group-based training sessions at the outpatient clinic (group size varies between 8 to 12 participants) under supervision of physical therapists and exercise specialists. All physical therapists and exercise specialists involved in this trial are specialised in CR and have been trained in motivational interviewing. Patients receive an individually tailored training programme on a treadmill or an electromagnetically braked cycle ergometer. Therefore, the total number of training sessions will vary among patients according to the clinical algorithms [26]. The physical therapist documents training attendance. In the last training session, the training programme is evaluated and patients are encouraged to continue physical activities at home. After 3 months, all treatment modules of the CR programme are evaluated by a nurse specialist at the outpatient clinic.

### Intervention group (cardiac telerehabilitation)

#### Web application

The core component of the study intervention is a secured, personalised, patient-centred web application. Safety and privacy are warranted by using encryption and signature layers. This platform enables patients to:- Register and adjust rehabilitation goals, training goals and treatment modules- Upload and review exercise training data- Upload and review daily physical activity data- Perform video consulting with physical therapists- Permit relevant pre-specified caregivers (e.g. cardiologist, psychologist, general practitioner or informal carers) to have access to the abovementioned data.

After the randomisation procedure, patients select and specify their treatment goals during the second part of the intake procedure with the nurse specialist. These goals will be registered in the web application by the patient and the investigator. During this meeting patients are instructed to use the platform on their personal computer, and to provide access to other caregivers. Patients also receive a heart rate monitor (Mio Alpha, Physical Enterprises Inc., Vancouver, British Columbia, Canada) and accelerometer (ActiGraph wGT3x-BT, Actigraph LLC, Pensacola, Florida, USA).

#### Exercise training

Patients in the intervention group start their CR programme with six supervised training sessions in the outpatient clinic, similar to patients in the control group. During these sessions, they are instructed about (home-based) training and training intensity, the use of their heart rate monitor and accelerometer and the transfer of data to the web application. In addition, patients are counselled on the training modality (e.g. cycling, walking/running) they prefer to incorporate in their exercise programme at home.

After six training sessions, exercise training is transferred to the home environment. Exercise training is continued in the hospital when home-based training is considered unsafe by the CR cardiologist or when the patient prefers to continue training in the hospital. If exercise training is transferred to the home environment, exercise training targets (i.e. frequency, session duration and time in heart rate zone) and physical activity targets (time spent at a moderate or high activity level, using a modified version of the algorithm proposed by Sasaki et al. [27]) are recorded in the web application. A weekly video consultation with the physical therapist is scheduled until CR is completed and evaluated at the outpatient clinic after three months. During these video consultations, both the exercise data and physical activity data are evaluated and targets are adjusted if needed.

If exercise training is not transferred to the home environment, patients continue exercise training at the outpatient clinic. Similar to the control group, the total number of training sessions is based on the clinical algorithms. However, physical activity is monitored at home, using data from the accelerometer. During the exercise training sessions at the hospital, exercise and physical activity targets are evaluated, and adjusted in the web application if needed.

#### Telemonitoring guidance

Patients are instructed to wear a wrist-worn heart rate monitor with a display (Mio Alpha) and a hip-worn accelerometer without a display (Actigraph wGT3x-BT) during all training sessions. For exercise training sessions, heart rate data is transferred to the accelerometer by Bluetooth and stored locally. To assess physical activity behaviour, patients are instructed to wear the accelerometer four days a week during daytime, of which at least one day during weekends. They upload exercise training and physical activity data to the web application weekly, by connecting the accelerometer to their personal computer using a USB-connection. On the web application, patients and their physical therapist (as well as other people who have access to the platform) can review the training and physical activity data graphically. A weekly video consultation with the physical therapist takes place via the web application.

These consultations are based on semi-structured interviews, in which the principles of motivational interviewing are applied. Motivational Interviewing is a psychosocial intervention technique to approach people engaged in behavioural change and tries to expose ambivalence between current and future behaviour [28–30]. The goal of Motivational Interviewing is to increase patients’ intrinsic motivation and encourage self-efficacy, in order to establish and maintain behavioural change.

During a video consultation, the physical therapist first checks whether the training sessions lead to symptoms, injuries or adverse events. Second, the physical therapist verifies whether patients adhere to their training schedule. Training frequency, session duration and intensity are recorded on the web application and are evaluated during the consultation. Together with the physical therapist, patients can adjust their training schedule if a structural problem prevents them from adhering to their schedule. Third, the physical therapist and patient review the physical activity data. They evaluate whether the physical activity targets have been reached (i.e. a desired amount of minutes spent at a moderate or high activity level). During the video consultation, the physical therapist identifies possible motivational issues, which can be exposed and addressed using motivational interviewing. We expect a video consult will take between 10 and 20 min.

#### Follow-up and on-demand coaching

During the final video consultation, the training period is evaluated and the individual exercise and physical activity targets are updated. These targets are recorded in the web application. Patients are instructed to use the heart rate monitor and accelerometer during the entire study period and to upload exercise training and physical activity data to the web application every week.

After the evaluation of the CR programme, coaching is performed on-demand. The web application evaluates the exercise training and physical activity data every four weeks and generates an alert in the following circumstances:- Non-compliance: not uploading sensor data for ≥ 4 weeks.- Reduced exercise training: a decrease of ≥ 50% in the time spent in a specified heart rate zone (average per week)- Reduced physical activity: a decrease of ≥ 50% in the time spent in moderate to vigorous activity zone (average per day).

If an alert is generated, a video consultation is scheduled. In this video consultation, exercise and physical activity targets are evaluated and adjusted similarly to previous video consultations. If the targets are adjusted, the patient updates the targets in the web application.

### Outcome measures

The primary outcome measure is physical activity level, assessed at baseline, three months and twelve months. Secondary outcome measures are physical fitness, Body Mass Index (BMI), blood pressure, health related quality of life, anxiety and depression and patient empowerment, assessed at baseline and at three and twelve months. Other secondary outcome measures include patient satisfaction (assessed at twelve months) and cost-effectiveness (assessed at three, six, nine and twelve months). Health literacy is only assessed at baseline. An overview of the study design is provided in Fig. 1.

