**Methods:**

This randomised controlled trial compares cardiac telerehabilitation with centre-based cardiac rehabilitation in patients with coronary artery disease. We randomise 300 patients entering cardiac rehabilitation to centre-based cardiac rehabilitation (control group) or cardiac telerehabilitation (intervention group). The core component of the intervention is a patient-centred web application, which enables patients to adjust rehabilitation goals, inspect training and physical activity data, share data with other caregivers and to use video consultation. After six supervised training sessions, the intervention group continues exercise training at home, wearing an accelerometer and heart rate monitor. In addition, physical activity levels are assessed by the accelerometer for four days per week. Patients upload training and physical activity data weekly and receive feedback through video consultation once a week. After completion of the rehabilitation programme, on-demand coaching is performed when training adherence or physical activity levels decline with 50% or more. The primary outcome measure is physical activity level, assessed at baseline, three months and twelve months, and is calculated from accelerometer and heart rate data. Secondary outcome measures include physical fitness, quality of life, anxiety and depression, patient empowerment, patient satisfaction and cost-effectiveness.

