We hypothesize that cardiac telerehabilitation using modern communication methods and multiple evidence-based behavioural change strategies including relapse prevention, will result in improved self-management skills and sustainable behavioural change. We expect this will translate to a superior increase in physical activity levels when compared to centre-based CR. Therefore, the objective of the SmartCare-CAD trial is to investigate whether cardiac telerehabilitation using modern technology and multiple behavioural change strategies results in better long-term physical activity levels than centre-based CR in patients with CAD. For telerehabilitation, a personalised patient-centred web application is used, comprising remote monitoring of exercise and physical activity behaviour and on-demand video consultation. In addition, both strategies will be compared with respect to physical fitness, modifiable cardiovascular risk factors, quality of life, anxiety and depression disorders, patient empowerment, patient satisfaction and cost effectiveness.

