### Sample size calculation

Adopted from Kraal et. al [24], we calculated sample size for the primary outcome measure –physical activity energy expenditure (PAEE) – assuming PAEE in healthy subjects was 4.0 ± 1.2 MJ/day [25]. If the difference in the primary outcome measure between the intervention and control groups is 10%, 143 subjects need to be included in either group (power = 0.8 and alpha =0.05). Taking into account loss to follow-up, 150 subjects are included in both groups.

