### Statistical analysis

All analyses will be performed on an intention-to-treat basis. Descriptive statistics will be used to report demographics and baseline characteristics. Between-group differences and within group differences in the outcome measures will be evaluated using multivariate analysis of variance (MANOVA). Pearson’s correlation coefficient (r) will be applied to quantify relations between changes in variables. For all statistical comparisons, the level of significance will be set at p < 0.05. Analyses will be carried out in the statistical software package SPSS (version 22).

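### The primary outcome is stated at 3 and 12 months with no deciding visit, so a difference seen only at 3 months can give a positive result in a trial about long-term activity

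*Protocol article*

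**What the plan says.** The Outcome measures section of the protocol article states: "The primary outcome measure is physical activity level, assessed at baseline, three months and twelve months". The Methods part of the abstract repeats this and ranks neither post-baseline visit above the other: "The primary outcome measure is physical activity level, assessed at baseline, three months and twelve months, and is calculated from accelerometer and heart rate data".

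The Background gives the objective as finding out whether telerehabilitation "results in better long-term physical activity levels than centre-based CR in patients with CAD". The Discussion repeats that aim. Neither place ties long-term to a visit.

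The Sample size calculation names PAEE as the primary outcome measure, "assuming PAEE in healthy subjects was 4.0 ± 1.2 MJ/day", and continues: "If the difference in the primary outcome measure between the intervention and control groups is 10%, 143 subjects need to be included in either group". No visit is named. The stated power is 0.8, with alpha at 0.05.

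The Statistical analysis section says: "Between-group differences and within group differences in the outcome measures will be evaluated using multivariate analysis of variance (MANOVA"). It then adds: "For all statistical comparisons, the level of significance will be set at p < 0.05". It gives no contrast, no order of visits and no rule for what counts as success.

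**The concern.** An endpoint definition includes its time point. Here the article gives the definition itself, with two post-baseline visits on an equal footing, and sets it beside an objective that concerns only the later period.

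The two visits can plausibly disagree. At 3 months the intervention arm is finishing a phase of weekly video consultations. From then to 12 months, coaching is triggered only by alerts (Follow-up and on-demand coaching). The Background itself notes that activity often falls after a successful programme. A gain that fades is the failure this trial was built to detect, and the stated plan does not stop such a gain from being reported as a positive primary result.

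At stake is what a positive trial would mean. Depending on how the analysis is run, there is also a question about the error rate of the primary claim.

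**Working it through.** **1. Reproduce the plan's figure.** Inputs from the Sample size calculation: mean 4.0 and SD 1.2 MJ/day, difference 10% = 0.4 MJ/day, power 0.80, alpha 0.05.

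n per arm = 2 × (z₀.₉₇₅ + z₀.₈₀)² × SD² / difference² = 2 × (1.960 + 0.842)² × 1.2² / 0.4² ≈ 141.3, so 142. The t-based solution is 142.2, which rounds up to the stated 143. A one-sided test would need 112 and does not match. The stated size is therefore one two-sided comparison of two means at one unnamed visit.

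**2. Set up the transient-effect case (assumed).** True difference 0.4 MJ/day at 3 months, exactly zero at 12 months, 143 per arm, SD 1.2 at both visits. The article gives no correlation r between the 3- and 12-month values, so 0.3, 0.5 and 0.7 are used. The standardised shift at 3 months is

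δ = 0.4 / (1.2 × √(2/143)) = 2.819, so δ² = 7.944.

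**3. Chance of a positive result under three readings of the stated analysis.**

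- *Separate tests:* success if either visit has p < 0.05. The probability is 1 − P(|Z₁| < 1.96 and |Z₂| < 1.96), with (Z₁, Z₂) bivariate normal, means (δ, 0) and correlation r.
- *Two-visit MANOVA omnibus test (Hotelling T²):* non-centrality λ = δ² / (1 − r²), F with 2 and 283 degrees of freedom. λ = 8.73, 10.59 and 15.58 for r = 0.3, 0.5 and 0.7.
- *Group effect averaged over the two visits:* shift δ / √(2 + 2r) = 1.748, 1.627 and 1.529, tested against ±1.96.

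| Reading | r = 0.3 | r = 0.5 | r = 0.7 |
|---|---|---|---|
| Separate tests, either visit | 0.817 | 0.821 | 0.826 |
| MANOVA omnibus | 0.752 | 0.834 | 0.950 |
| Average over visits | 0.416 | 0.370 | 0.333 |
| 12 months only | 0.05 | 0.05 | 0.05 |

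**4. False-positive rate with no effect at either visit.** Two separate tests at 0.05, from the same bivariate formula with δ = 0: 0.0951, 0.0907 and 0.0835 for r = 0.3, 0.5 and 0.7. A single omnibus test, or a single test of the average, stays at 0.05.

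**5. Effect of naming one visit.** With 12 months as the only primary comparison, power is 0.80 at 143 per arm and 0.82 at 150. If both visits were kept as alternative routes to success at a Bonferroni 0.025 each, the same formula gives 172 per arm, and power per visit at 143 falls to 0.72.

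**The case against.** The strongest reply is that this is a condensed article. The full protocol or the SAP may name the visit, and details of MANOVA contrasts are commonly left there. The sentence on the primary outcome can also be read as an assessment schedule, since it lists baseline too, and 12 months is the only scheduled visit that fits a long-term aim. All of this is fair. It shows which visit was probably meant, but not that the article fixes it. The article sets out the endpoint, the powered difference and the significance rule, and none of them is tied to 12 months.

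A reader might infer that the plan's false-positive rate is necessarily above 5%. The article does not support that. The method it names is MANOVA, and one omnibus test over the visits holds 5%. Inflation arises only if the visits are tested separately.

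A reader might also take the 75-95% as the plan's operating characteristic. It belongs to one reading. A repeated-measures group effect averaged over visits gives a much lower 33-42%. The on-demand coaching is meant to sustain the difference, so an effect that vanishes completely is a stress case and not a forecast.

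Nor is the use of both PAEE and physical activity level a contradiction, because the Measurements section says the second is determined by the first.

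**Conclusion.** The point holds: the article does not say which visit decides the primary outcome, and under each of the three readings examined a difference confined to 3 months can yield a positive primary result. The probability is about 82-83%, 75-95% or 33-42% according to the reading, against 5% if only 12 months counts. These figures rest on a full 0.4 MJ/day effect at 3 months, none at 12 months, equal SDs, 143 per arm, and assumed correlations of 0.3 to 0.7. The familywise error of about 8.3-9.5% is conditional on separate tests at 0.05. The main defect is the mismatch between the objective and the success criterion; alpha inflation is a possible further consequence.

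**What to change.** State in the protocol or SAP, before database lock: *The primary analysis is the between-group difference in PAEE (MJ/day) at 12 months, adjusted for baseline PAEE, at two-sided alpha 0.05. The 3-month difference is secondary. Within-group changes are descriptive.*

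This settles the visit, the quantity and its unit, and how baseline enters, which the article leaves open between a level and a change. It matches the stated objective, needs no new data and leaves the sample size at 143 per arm before loss to follow-up (150 after). The only cost is that the 3-month result loses primary status.

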**Fig. 1 Fig1:**
[figure not shown]
Flowchart of the study design. *KvL-H* Kwaliteit van Leven bij Hartpatiënten, *GAD-7* Generalized Anxiety Disorder, *PHQ* Patient Health Questionnaire, *PAM* Patient Activation Measure, *SBSQ-D* Set of Brief Screening Questions - Dutch, *CQI* Consumer Quality Index

### Measurements

#### Physical activity level

Physical activity level (PAL) is determined by physical activity energy expenditure (PAEE), as described previously [31]. PAL is calculated from data from the accelerometer (ActiGraph wGT3x-BT) and a chest-strap heart rate monitor without a display (Polar H7, Polar Electro Oy, Kempele, Finland). The data of the heart rate monitor are transmitted to the accelerometer through Bluetooth. Patients are required to wear the sensors during daytime for an assessment period of four days, which includes two weekend days. During these days, the wrist-worn heart rate monitor (Mio Alpha) cannot be worn. Patients are blinded for both physical activity (accelerometry) and heart rate data.

After the assessment period of four days, patients in the intervention group upload the data to the web application. Patients in the control group return their sensors to the investigator. Accelerometry data (40Hz sample frequency) are synchronized with heart rate data (1Hz sample frequency) and resampled into one minute epochs. The energy expenditure estimation model developed by Kraal et al. is applied to calculate PAL [31].

#### Physical fitness

Physical fitness is assessed by a symptom limited exercise test. The maximal workload (in Watts) and percentage of the predicted value are calculated after completion of the test. The test will be performed on a cycle ergometer (Lode Corrival, Groningen), using an individualised ramp protocol aiming at a total test duration of 8–12 min. Patients are instructed to maintain a pedalling frequency of 70 rounds per minute. A twelve lead ECG is registered continuously.

#### Body mass index and blood pressure

The investigator measures length, weight and blood pressure prior to the symptom limited exercise test. Body mass index is defined as bodyweight divided by the square of ones height (in kilograms per square metre). Blood pressure is recorded using an automatic digital sphygmomanometer, using a standard cuff size for an arm circumference of 22–32 cm as well as an oversized cuff for larger arm circumferences according to the manufacturer's guidelines. Patients are instructed to adopt an upright sitting posture with the right arm on a table, the palm facing upwards, with uncrossed legs and the feet placed on the floor throughout the procedure. The cuff is applied to the right upper arm so that the bottom edge of the cuff is positioned 1–2 cm above the elbow joint and the cuff at heart height. At least two measurements are taken with a 5-min interval and the second blood pressure reading is used in the data analysis [32].

